### Analytical methods

Analysis and reporting will be in line with the CONSORT (Consolidated Standards of Reporting Trials) extension for randomised pilot and feasibility trials [49]. Patient-reported outcome scores from questionnaire data will be calculated based on the developers’ scoring manuals, and missing and erroneous items will be handled according to these instructions. Continuous measures will be presented as means and standard deviations or medians and ranges depending on their distribution. Categorical data will be presented as frequencies and proportions, with 95% confidence intervals.

The study will assess the following primary outcomes:Recruitment: % of those eligible and approached who consent to randomisation at invitation.Retention: % completing follow-up questionnaire approximately 4–8 weeks after baseline questionnaire.

We will describe the primary outcome variables across socioeconomic position quantiles.

Descriptive statistics will be used to report the secondary outcomes of interest.

Qualitative interviews will be analysed using inductive thematic analysis, as described by Braun and Clarke[50]. Transcripts will be read twice to gain familiarisation and sections of text coded by assigning descriptive labels. Codes will be grouped based on shared properties and themes identified. All transcripts will be independently coded by two researchers, the CI and another qualitative researcher. Codes will be discussed to maximise rigour and reliability, to identify areas of discrepancy and to refine the coding system. NVivo software will be used to aid analysis. Data collection and analysis will be conducted concurrently, employing an iterative approach. The sample size for the qualitative phase will be determined by reaching theoretical theme saturation [51].

### Data management

Clinical data will be stored using REDCap [52]. REDCap is a secure, web-based electronic data capture system designed for the collection of research data. Although the system has been developed (and it is supported) by Vanderbilt University, the University of Bristol (UoB) has set up its own infrastructure to host the REDCap application so that all elements reside within UoB. REDCap is used solely for anonymised clinical data linked by a participant ID. Data are stored in a secured UoB server subject to standard UoB security procedures. The full database is backed up daily. Additionally, changes are logged every 5 min. A disaster/recovery plan is in place as part of the service-level agreement (SLA) we have with IT services. Data entry can be performed by accessing the REDCap application directly or via surveys. In order to access the application directly, users will be added to the system following request to the CI. It is the CI’s responsibility to add the user to a specific project and role.

Qualitative data will be collected as encrypted digital audio files and then transcribed into word files through secure University of Bristol-approved transcription services. Anonymised transcripts will be uploaded to NVivo software for analysis, and audio files will be destroyed. No one other than the CI and the transcription service will be allowed access to the qualitative audio files due to the risk of participant identification.

### Decision whether to progress to full RCT

A quantitative dashboard with green/amber/red thresholds is proposed to guide decision-making following this study on progression to a full-scale RCT (Table 4). Achieving all green targets would almost certainly mean proceeding to the full trial, whereas achieving predominantly red targets would almost certainly indicate that a full-scale RCT is not feasible.

**Table 4 Tab4:**
[figure not shown]
Green/Amber/Red progression criteria

Analysis of questionnaire responses and thematic analysis of the qualitative interview data regarding acceptability of the intervention and trial processes will further assist with decision-making on progression. Progression will only occur if the majority of participating renal patients and their families report that the intervention and trial processes are acceptable.

### Monitoring

The Trial Management Group (TMG) will comprise of the CI ([name]), coinvestigators ([name], FC, SM), the intervention HCPs and patient representatives. The TMG will meet approximately once each month in the first 6 months, then 6 monthly to review progress, with potential for additional ad hoc meetings, as required/indicated. These meetings will be chaired by the CI. Participants will have the opportunity to join the meetings in person or virtually.

The Trial Steering Committee will be chaired by an independent member and comprise a minimum of four additional independent members (covering expertise in transplantation and clinical trials and including people who have received a kidney transplant or donated a kidney). The CI ([name]) will also be a member of the TSC. Observers may also attend, as may other members of the TMG or members of other professional bodies, at the invitation of the chair. The TSC will meet for the first time by month 6 of the trial and then at least every 6 months until the trial closes. For this feasibility trial, the TSC will also have responsibility for data monitoring. For discussions regarding data monitoring, the CI and other members of the TMG will be asked to leave the room so that the data monitoring is only undertaken by the independent members of the TSC, without the influence of those involved in the delivery of the trial.

### Harms

Due to the nature of advanced kidney disease and its treatments, serious adverse events (SAEs) would be expected to occur throughout the course of the disease and therefore this study. These expected SAEs include the following:Abnormal electrolyte and haematological laboratory results that can be explained directly or indirectly by their advanced kidney diseaseHospital admissions — elective and emergency — that can be explained directly or indirectly by their advanced kidney diseaseHospital admissions for elective procedures with the exception of a kidney transplantInfections and cardiovascular events that can be explained directly or indirectly by their advanced kidney diseaseCommencement of dialysisDeath that can be explained directly or indirectly by their advanced kidney disease

These expected SAEs do not require reporting to the sponsor but will be recorded in the participant’s medical records. However, anything not in the above list, or anything the principal investigator or CI deems unexpected, must be reported to the sponsor.

All reportable SAEs occurring from the time of consent until 30 days after the end of the trial must be documented and emailed securely to the sponsor within 24 h of the research staff becoming aware. The CI will report any SAE that is related to the research procedures and unexpected to the research ethics committee and the sponsor within 24 h of becoming aware of the event.

For each SAE, the following information will be collected as follows:Full details in medical terms and case descriptionEvent duration (start and end dates, if applicable)Action takenOutcomeSeriousness criteriaCausality (i.e. relatedness to trial/intervention), in the opinion of the investigatorWhether the event would be considered expected or unexpected

Any change of condition or other follow-up information should be securely emailed to the sponsor as soon as it is available or at least within 24 h of the information becoming available. Events will be followed up until the event has resolved or a final outcome has been reached.

Each SAE must be reported separately. Any change of condition or other follow-up information relating to a previously reported SAE should be documented and emailed securely to the sponsor as soon as it is available or within at least 15 days of the information becoming available to the research team. Events will be followed up until the event has resolved or a final outcome has been reached.

All other adverse events will be reported to the CI by sites via an online AE form, and a summary report will be submitted to the TSC on a regular basis.

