The clinician letter to potential donors is a standard practice in Norway [32] but has never been formally evaluated for effectiveness or for potential harms such as potential donors feeling pressure to donate. The home-based patient and family education intervention has been evaluated in randomised controlled trials (RCTs) in the Netherlands and the USA [33, 34]. In the study from the Netherlands, there were more LDKTs in the experimental group compared with the control group (17/39 vs. 4/41, *p* = 0.003) [33]. In the USA trial, compared to control, more patients in the home-based education group had LDKTs (30.4% vs. 52.4%, *p* = 0.013) [34]. However, the healthcare systems and populations of these countries are not directly comparable to those of the UK. It is not known if intervention delivery is feasible in the NHS, if the intervention is cost-effective in the UK or if it reduces inequity in living-donor kidney transplantation which the larger planned RCT aims to determine. The intervention components have not been evaluated together as a single intervention that targets multiple barriers to living-donor kidney transplantation.

This feasibility trial is designed to gather information on the logistics of delivery, acceptability and risk of harm of the developed intervention and to determine if it would be possible to conduct a full-scale trial. A parallel process evaluation [35] will investigate the acceptability, implementation and mechanisms of impact of the intervention.

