#### Intervention component 3: home-based education and family engagement

The home visit will be undertaken by two intervention HCPs who will deliver the education and engagement package approximately 2–4 weeks after the first meeting. The home visit can take place at any day and time that suits the participant and their guests; this includes evenings and weekends. In exceptional cases, a second home visit may be required.

The home education and engagement session will cover the following: kidney disease (specific to the participant’s disease); dialysis; transplantation — deceased-donor and living-donor transplantation; living kidney donation; and open discussion.

The HCPs will share their work telephone number and work email addresses with participants so that they can be contacted for further advice and support if required at any time during the trial. If requested, a second home visit covering all or part of the content of the first visit can be delivered.

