### Data collection

Trial participants will have two standard study contacts and one optional qualitative contact:BaselineFollow-up: Questionnaire completion 1–3 days after the home visit or for those not receiving the intervention in the control arm, 4–8 weeks after the baseline assessment.Qualitative: After the home visit, some purposively sampled patient participants will be invited to consider participating in qualitative interviews.

Clinical and laboratory data will be extracted from hospital medical records by the research nurses. The data collected are reported in hospital medical records and do not require interpretation. Patient-reported outcome data will be collected through questionnaires self-completed by participants. Participant experience of the trial and intervention will be collected through qualitative interviews. Compliance with the intervention will be recorded by the intervention HCPs against a checklist.

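### Harms are recorded as staff become aware of them, and the intervention arm has more staff contact, so adverse event counts may not be comparable between arms

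*Protocol article*

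**What the plan says.** On capture, the Harms section sets a reporting window: "All reportable SAEs occurring from the time of consent until 30 days after the end of the trial must be documented". The trigger is awareness: such events must be "documented and emailed securely to the sponsor within 24 h of the research staff becoming aware". For the remainder, "All other adverse events will be reported to the CI by sites via an online AE form". A list of expected serious events is exempt: "These expected SAEs do not require reporting to the sponsor but will be recorded in the participant’s medical records".

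On contact, the Data collection section states that "Trial participants will have two standard study contacts and one optional qualitative contact". The two standard contacts are baseline and a self-completed follow-up questionnaire. The questionnaire falls a few days after the home visit in the intervention arm and, "for those not receiving the intervention in the control arm, 4–8 weeks after the baseline assessment". The Intervention sections add a telephone call, a meeting and a home visit by two professionals. A second home visit is possible, and contact details are shared "so that they can be contacted for further advice and support if required at any time during the trial".

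On purpose, the Background says the trial is "designed to gather information on the logistics of delivery, acceptability and risk of harm of the developed intervention".

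**The concern.** When events are recorded only as someone hears of them, the number recorded depends on how often someone is in a position to hear. Here that differs by arm, and the Allocation section says that neither participants nor those delivering the intervention can be blinded. A participant who mentions distress, family conflict or a minor event during a home visit has told a member of the trial team. A control with the same experience has no equivalent conversation, and no harm item is listed in the questionnaire that the control completes.

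At stake is the harm information that the trial sets out to gather. The independent members of the Trial Steering Committee carry out data monitoring, and a regular adverse event summary goes to that committee. The findings shape the full-scale trial, and the Access to data section foresees requests for meta-analysis. A difference in counts could reflect frequency of contact rather than risk.

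**Working it through.** The plan gives no figure for harm detection, so there is none to reproduce. The check compares what each arm receives after randomisation.

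**Intervention arm only**
- Telephone call within 1 week (Intervention).
- Meeting within 2–4 weeks of recruitment (Intervention component 1).
- Home visit by two professionals about 2–4 weeks after that meeting, with a second visit possible (Intervention component 3).
- Open telephone and email line (Intervention component 3).
- For some participants, an optional interview after the home visit (Data collection).

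**Control arm only**
- A research nurse's check at the end of the study on whether any intervention element was received from elsewhere (Mixed-methods process evaluation).

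**Both arms**
- Self-completed questionnaire at about 4–8 weeks. The contents in Table 3 are knowledge, social support, activation, health literacy, transplant preference and beliefs, conversations with family and friends, and quality of life. There is no adverse event item.
- Research nurse extraction from hospital records at 12 weeks. Table 3 lists listing status and transplant, comorbidities, stage of kidney disease, date and cause of death, body mass index, laboratory items and number of donors under assessment. There is no adverse event item.
- Registry linkage, with consent, for start of kidney replacement therapy, transplant and death (Outcome data).

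Scheduled staff conversations after randomisation therefore number at least 3 in the intervention arm. Controls have one self-completed form and the end-of-study check. The intervention professionals also sit on the Trial Management Group, so what they hear can reasonably be taken as known to the trial; this is an inference, as the article does not define research staff.

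**Which events are exposed.** Deaths and transplants are extracted or linked in both arms. Admissions stand in the hospital record in both arms, although Table 3 does not name them as an item. Many of these are on the expected list and are not reported to the sponsor at all. What remains is mainly unexpected serious events other than transplant, and non-serious events. These depend most on somebody being told.

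**Illustration of size.** Every detection rate and risk here is an assumption. With equal true risk r in both arms, n per arm, and detection d_I (intervention) and d_C (control):
- Expected recorded events = n × r × d.
- Apparent risk ratio = d_I / d_C, which does not depend on r.

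Take n = 30 (Sample size section), r = 20% and d_I = 90%. The intervention arm then records 30 × 0.20 × 0.90 = 5.4 events. For controls:
- d_C = 90%: 30 × 0.20 × 0.90 = 5.4; ratio 0.90/0.90 = 1.0.
- d_C = 70%: 30 × 0.20 × 0.70 = 4.2; ratio 0.90/0.70 = 1.29.
- d_C = 50%: 30 × 0.20 × 0.50 = 3.0; ratio 0.90/0.50 = 1.8.
- d_C = 30%: 30 × 0.20 × 0.30 = 1.8; ratio 0.90/0.30 = 3.0.

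**Reporting window.** It closes at a trial date, not a participant date. Assume that recruitment lasts about 26 weeks (inferred from the 6-month list refresh in the Recruitment section) and that the trial ends at the last participant's week 12. Thirty days is 30/7 = 4.3 weeks. The first recruit is then covered for 26 + 12 + 4.3 = 42.3 weeks and the last for 12 + 4.3 = 16.3 weeks. With concurrent 1:1 allocation within site, this variation falls on both arms alike and does not itself bias the comparison. It matters only because, after week 12, no data collection common to both arms is listed apart from registry linkage, while the open line continues in one arm.

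**The case against.** The strongest reply has four parts.

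1. Controls are not out of sight. They have the questionnaire, the 12-week record extraction, the end-of-study nurse check and registry linkage. This stands, and it rules out the tempting stronger reading that only the intervention arm has staff contact, so that harms will be over-detected there and missed in controls. More contact gives fuller detection, which is not over-detection, and nothing in the article shows that control events will in fact be lost. The gap is that none of these control-arm routes is described as asking about adverse events.

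2. No by-arm harm comparison is planned. Harms are not among the outcomes in Table 1, secondary outcomes are descriptive, and the Access to data section says the study was not designed for meaningful analysis of quantitative outcomes. This limits the consequence, since no test is distorted. It does not remove the problem, because risk of harm is a stated purpose and a summary can mislead without a test.

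3. A journal article condenses the full protocol, Table 3 is called a summary, and the schedule figure is not reproduced in the text read here. A common adverse event prompt may exist elsewhere. That is possible, but the article describes the reporting routes at length and itemises follow-up content, and the mechanism it states is uneven.

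4. Adding an adverse event field to the record extraction alone would strengthen the source that is already even between arms. This stands too: events that never reach hospital notes need a question put to the participant. Nor would participants' records show the harm named in the Background, pressure felt by potential donors. The planned interviews are the better route for that.

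**Conclusion.** The point holds as a risk of unequal ascertainment. Capture depends on awareness or on site reports, the unblinded intervention arm has at least three more scheduled staff contacts plus an open line, and the listed follow-up contains no adverse event enquiry common to both arms. Counts of non-serious or unexpected events not visible in records or registries may be fuller in the intervention arm and should not be compared between arms as they stand.

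The size is unknown. It could be nil for deaths, transplants and admissions. The ratios of 1.0 to 3.0 above show how the result moves with assumed detection rates; they are not estimates for this trial. The conclusion assumes that no identical enquiry is set out in a fuller protocol or in the schedule figure. It does not touch the primary outcomes of recruitment and retention, and it does not rest on the length of the reporting window.

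**What to change.** - Add the same adverse event question to the existing 4–8 week questionnaire in both arms, covering the time since consent.
- Add an AE/SAE field to the existing 12-week record extraction in both arms, covering consent to week 12.
- Base any by-arm harm summary, including one for the Trial Steering Committee, on these two common sources from consent to week 12. State that the questionnaire covers only those who return it and only up to the day they complete it.
- List separately, by source, events learned only through intervention contacts or after week 12.
- Leave expedited reporting of serious events unchanged.

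The cost is a slightly longer questionnaire and extraction for 60 participants, with no new visit. If the full protocol already contains such an enquiry, one sentence in the Harms section and a line in Table 3 would settle the point.

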### Auditing

All trial-related documents will be made available on request for monitoring and audit by the University of Bristol, the Research Ethics Committee and available for inspection by other licensed bodies. Monitoring and audits undertaken by the University of Bristol, under their remit as sponsor, or individuals appointed responsibility for monitoring on their behalf, will ensure adherence to good clinical practice and the UK policy framework for health and social care research. Remote monitoring will be conducted based on information submitted by sites and analysis of the trial database. Site visits will then be initiated using a risk-based approach.

The University of Bristol Research Governance Department also regularly reviews its research portfolio. The University of Bristol has a service-level agreement with University Hospitals Bristol NHS Foundation Trust, whereby the trusts monitor 10% of the university’s sponsored studies. University Hospitals Bristol NHS Foundation Trust has a standard operating procedure (SOP 014 Monitoring and Oversight of Research) available at http://www.uhbristol.nhs.uk/research-innovation/for-researchers/run-a-study-and-closedown/monitoring/.

### Confidentiality

The University of Bristol will be the data custodian. All data held in Bristol will conform to the University of Bristol Data Security Policy and in compliance with the Data Protection Act 1998. Data will be managed according to the University of Bristol’s Research Data Management policy: http://www.bristol.ac.uk/research/environment/governance/research-data-policy/.

### Access to data

Anonymous research data will be stored securely and kept for future analysis. Data will be uploaded to the University of Bristol’s Research Data Repository: https://data.bris.ac.uk/data/.

The final qualitative and quantitative dataset will be accessible by the CI, the coinvestigators, the trial statistician and the TSC. Local PIs will not have access to final dataset unless formally requested and approved by the TSC. The anonymised qualitative data transcripts will be suitable for sharing with other researchers who may wish to undertake a thematic synthesis or analyse the interviews using a different methodology to the one used in this study. Consent for the sharing of the interview transcripts to other researchers will be explicitly sought from interviewees prior to the interview, and this confirmed with the interviewee following the interview. Transcripts will be anonymised with all personal identifiers and possible identifiers redacted. This includes details that may identify other people mentioned in the interview, e.g. clinicians and family members. Participants will be informed that transcripts will be stored in accordance with the Data Protection Act [53], and they will be asked to confirm in writing that they have understood this. If consent for sharing is not provided, the data will be used by the primary research team only. Due to personal issues being discussed, we cannot rule out the risk of reidentification therefore as a double safeguard access to these transcripts will be controlled. Requests for controlled data through the University of Bristol are referred to an appropriate Data Access Committee (DAC) for approval, before data can be shared with bona fide researchers, after their host institution has signed a Data Access Agreement. The university’s DAC comprises the following: assistant director of research services (library), information rights officer (FOI, data protection), head of research governance (ethics), assistant director IT services (data security), research contracts (if commercially sensitive), academics, e.g. the PI. The procedure for accessing data can be found here: https://www.bristol.ac.uk/staff/researchers/data/accessing-research-data/.

If the DAC grants access to the data, a University of Bristol Data Access Agreement is drawn up and signed by the applicant, their host institution and the University of Bristol. The University of Bristol’s Research Data Service will oversee this.

The feasibility study has not been designed to allow meaningful analysis of the quantitative outcome data at this stage but rather to inform the design of a later randomised controlled trial. However, there have been two similar trials in other countries [33, 34], and data might be requested for meta-analysis. Data will be made available to other researchers on request after a period of exclusive use by the researchers of 5 years.

